#### Additional Outcomes

The quality of nursing care is assessed using a self-constructed questionnaire, which has been used in a previous pilot study by our research group. The quality of nursing care will be evaluated by the community nurses in Aalborg Municipality.

Another additional outcome is to assess how the citizens, who receive community nursing care from the nurses in the intervention group, experience nursing care prior to the intervention and after the intervention. Hence, the citizens will be interviewed twice during the study: prior to the intervention and after the intervention. As per the study by Kvale and Brinkmann [24], semistructured qualitative individual face-to-face interviews will be conducted with the citizens in the intervention group in the comfort of the own homes. The interviews will be conducted before the community nurses in the intervention group receive any special training and start using the intervention (prior) and again at follow-up (after). The interviews will be recorded and transcribed by researchers.

It is hypothesized that the ICM will be associated with a larger gain in HL in the intervention group, as the model is expected to increase citizens’ control of their own lives as it establishes a more solid knowledge and empowerment of their disease and health [25-27].

### Sample Size and Power Calculation

Sample size calculation for the primary outcome was performed in Stata (version 16; StataCorp). The intention is to detect a standardized mean difference in favor of the intervention based on Cohen *d*>0.8 [28]. Requiring a power of 80% and a significance level (1-sided) of 0.05, with 4 clusters given (2 in each alternative) and assuming a coefficient of variation in cluster size of 0.25 and intracluster correlation equal to 0.05, the required sample size is 37 participants in each arm (or an average of 18.5 participants in each cluster). With an expected loss-to-follow-up of 10%, the total required sample size is 41 in each arm (or an average of 20.5 in each cluster).

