**Methods:**

A quasi-experimental control group study including full economic evaluation with 6-month follow-up. Based on power calculation, a total of 82 participants will be included. Participants are assigned either the interactive communication model (intervention) or usual nursing care. It will be assessed if the model influences the level of health literacy and participants experience a higher health-related quality of life. Further, cost-effectiveness will be evaluated. Overall, the statistical methods will follow an intention-to-treat principle. Results will be presented in accordance with the Transparent Reporting of Evaluations with Non-randomized Designs guidelines for nonrandomized designs as well as the Consolidated Health Economic Evaluation Reporting Standards.

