### Allocation

Aalborg Municipality is comprised of 6 health care districts. However, due to practical reasons, a total of 2 districts declined to participate in this study. The remaining 4 districts are matched 1:1 in terms of geographical area (2 rural districts are matched and so are 2 urban), and each pair is then allocated so that one district is in the intervention and the other is in the control group. Coincidently, each pair also matches with the estimated level of social classes (judged by the municipality). Before allocation, all participants must have signed informed consent and conducted baseline measurements.

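### The stated 80% power rests on a normal reference distribution; with 2 districts per arm (2 degrees of freedom) a valid one-sided 5% test has about 50% power on the protocol's own inputs

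*Protocol article*

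**What the plan says.** Under Sample Size and Power Calculation, the target is a "standardized mean difference in favor of the intervention based on Cohen *d*>0.8". The error rates are given as "Requiring a power of 80% and a significance level (1-sided) of 0.05". The clustering is entered "with 4 clusters given (2 in each alternative"), "assuming a coefficient of variation in cluster size of 0.25 and intracluster correlation equal to 0.05". The result is that "the required sample size is 37 participants in each arm (or an average of 18.5 participants in each cluster"), and then "With an expected loss-to-follow-up of 10%, the total required sample size is 41 in each arm". The Abstract carries this forward: "Based on power calculation, a total of 82 participants will be included".

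The Allocation section confirms that whole districts are assigned. Four districts form two matched pairs, and "each pair is then allocated so that one district is in the intervention and the other is in the control group". The Analyses section plans multilevel generalized linear models, unadjusted and adjusted, and names no reference distribution for the arm effect.

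**The concern.** A design effect inflates the variance of the arm contrast for correlation within districts. It does not allow for the fact that the district-level variance must itself be estimated, here from four district means. With two districts per arm that leaves 4 − 2 = 2 degrees of freedom, where the normal and t critical values are far apart. If the sample size was derived with normal quantiles, the stated 80% power and the stated 5% level cannot both hold.

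The primary hypothesis is a significant gain in health literacy, and the Discussion and the Abstract's conclusions present the results as a basis for deciding on a large-scale study. A colleague told that power was 80% would give a non-significant result more weight than it deserves. If the normal critical value is used in the analysis, a significant result carries more false-positive risk than stated.

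**Working it through.** **Inputs (all from Sample Size and Power Calculation).** d = 0.8 (stated as greater than 0.8; the boundary is used), one-sided α = 0.05, power 80%, 2 clusters per arm, CV = 0.25, ICC ρ = 0.05, m = 18.5 per cluster.

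**1. Reproduce 37 per arm.** Without clustering, n₀ = 2(1.645 + 0.842)²/0.8² = 19.32 per arm. Two common design effects (DE) for unequal clusters, at m = 18.5:
- (a) DE = 1 + [(1 + CV²)m − 1]ρ = 1 + (1.0625 × 18.5 − 1) × 0.05 = 1.933.
- (b) Relative-efficiency form: DE = [1 + (m − 1)ρ]/[1 − CV²λ(1 − λ)], with λ = mρ/(mρ + 1 − ρ) = 0.925/1.875 = 0.493. This gives 1.875/0.9844 = 1.905.

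Solving 2m = n₀ × DE for m gives 37.7 per arm under (a) and 36.6 under (b). Form (b) rounds up to the stated 37.

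**2. Power at 37 per arm with the normal reference.** SE = √(2·DE/37) = 0.323 (a) or 0.321 (b), in SD units. The non-centrality is 0.8/SE = 2.475 or 2.493. Power = Φ(2.475 − 1.645) = 79.7%, or Φ(2.493 − 1.645) = 80.2%. The plan's figure is reproduced, and the normal quantile is what reproduces it.

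**3. Same inputs, t reference on 2 df.** The one-sided 5% critical value is 2.920. From the non-central t:

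| Analysed per arm | Power (a) | Power (b) |
|---|---|---|
| 37 | 49.7% | 50.1% |
| 41 | 51.2% | 51.6% |

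A simulated t test on district means (400,000 replicates, 18.5 per cluster on average, CV 0.25) gave 49.6% power and 5.0% type I error.

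**4. Detectable effect.** On 2 df, 80% power needs a non-centrality of 3.979. So d = 3.979 × 0.323 = 1.29 (a) or 3.979 × 0.321 = 1.28 (b).

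**5. Keeping 1.645 instead.** If the variance is estimated on 2 df, the one-sided type I error is P(t₂ > 1.645) = 12.1% (simulated 12.1%).

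**6. Ceiling with unlimited participants in these four districts.** As m grows, SE tends to √(1.0625 × 0.05) = 0.2305 (a) or √0.05 = 0.2236 (b). The non-centrality tends to 3.47 or 3.58, both below 3.979. Power tends to 71.3% or 73.3%.

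**7. Sensitivity.** The ICC values other than 0.05 are assumptions, taken with equal cluster sizes and d = 0.8.

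| ICC | Power at 18.5 per cluster | Limit as m grows |
|---|---|---|
| 0 | 71% | – |
| 0.01 | 65% | 99.8% |
| 0.03 | 57% | 88% |
| 0.04 | 54% | 80% |
| 0.05 | 51% | 73% |
| 0.10 | 40% | 51% |

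At ICC 0.05 and CV 0.25 under (a), d = 0.9 gives 57% at 18.5 per cluster. Its limit is 79%, or 81% with equal cluster sizes.

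**The case against.** **The calculation does use the clusters.** A reader might infer that the plan treated participants as independent, or that 37 is an arithmetic slip. Neither is so. The design effect nearly doubles the requirement, from 19.3 to 37 per arm, and 37 is what the inputs give under normal quantiles. Only the few-cluster reference distribution is left out.

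**The normal reference is inferred, and the test is not fixed.** The article says only that Stata was used. An analysis plan that is not shown may specify a degrees-of-freedom method for the multilevel model. Its absence from an article is no fault and is not raised here. What is challenged is the printed power. A small-sample method in the analysis would make the 80% wrong, and a normal reference would make the 5% wrong.

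**Adjustment and matching might add precision.** They might, and the figures above allow for no such gain. But adjustment creates no further districts, and respecting the two matched pairs leaves 1 degree of freedom, with about 30% one-sided power if matching removes no variance. Two degrees of freedom is the more generous choice.

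**The ceiling is conditional.** A reader might infer that no enrolment in these districts could ever reach 80%. That holds at d = 0.8 and ICC = 0.05. The protocol writes d as above 0.8. With an ICC of about 0.04 or less, or an effect somewhat larger than 0.8, very large clusters could reach 80%. This stands, but it does not help at the planned size.

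**The article is already cautious.** The Discussion frames the study as an early evaluation and lists selection bias and short follow-up as limitations. Nowhere does it say that a null result will be taken as evidence against the model. It does not mention the number of districts or limited power, so the stated 80% stands uncorrected.

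**Conclusion.** The concern holds for the stated power. On the protocol's own inputs, a one-sided 5% test that respects two districts per arm has about 50% power at 37 analysed per arm and 51–52% at 41. An 80% chance of detection needs an effect of about 1.3 SD. Keeping the normal critical value raises the one-sided type I error to about 12%.

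This assumes that the between-district variance is estimated from these four districts, that the pairs are not modelled, and that covariates bring no gain in precision. The shortfall at the planned size does not depend on the chosen ICC: for d = 0.8, power is about 71% even at ICC 0. The 71–73% ceiling does depend on d = 0.8 and ICC = 0.05 and should be quoted only with them.

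**What to change.** Keep 82 participants and make these changes:

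1. In Sample Size and Power Calculation, state that with two districts per arm and a small-sample reference on 2 degrees of freedom, power at one-sided 5% is about 50% for d = 0.8, and that 80% power corresponds to d of about 1.3.
2. State that at d = 0.8 and ICC = 0.05, further enrolment in these four districts cannot take power above about 71–73%.
3. In Analyses, tie the district-level comparison in the multilevel model to the same reference, so that the stated level and the stated power belong to one test.
4. In the Abstract's conclusions and the Discussion, describe the effectiveness result as preliminary, report the estimate with its interval to inform the large-scale study, name the small number of districts as a limitation, and say that a non-significant result will not be read as no effect.

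The cost is a less favourable stated power and a wider interval. For the same standard error, the two-sided 90% interval that corresponds to a one-sided 5% test widens by 2.920/1.645 = 1.78 times. No extra participants are needed.

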### Analyses

Overall, the statistical methods will follow an intention-to-treat principle [29]. Results from the trial will be presented in accordance with the Transparent Reporting of Evaluations with Non-randomized Designs guidelines for nonrandomized designs [30] as well as the Consolidated Health Economic Evaluation Reporting Standards [31]. Missing data will be subject to multiple imputations [32]. Data will be analyzed with Stata 16 software.

Between-group differences for both the primary and secondary outcomes of health-related quality of life and cost-effectiveness will be calculated by applying multilevel generalized linear models, and both an unadjusted and adjusted estimate controlling for meaningful baseline differences will be reported. To allow for evaluation of the impact of variability and parameter uncertainty, the economic evaluation will also report the results of one-way and probabilistic sensitivity analysis [33]. The probabilistic sensitivity analysis will be carried out using Excel (Microsoft Inc).

All data from the interviews will be analyzed using NVivo R1 (version 13.0; Lumivero). Inspired by Kvale and Brinkmann [24], the analysis will be conducted according to the following steps: (1) identification of key themes and definitions from theoretical framework, inspired by Braun and Clarke [34]. (2) Review of all data from the interviews to obtain an overall impression of the themes on how the citizens experience their level of HL and self-management, both prior to the intervention and after the intervention. (3) Design of code tree based on key definitions and concepts derived from the theoretical framework and interviews. (4) The researchers will discuss and revise the code tree to ensure intersubjectivity. (5) The first step of the coding process will be centered on gaining an overall understanding of the citizens’ perception of their level of HL and self-management, both prior to the intervention and after the intervention. (6) The next step will focus on widening the understanding beyond the citizens’ perception. What presents a challenge to their level of HL and self-management and what strengthens it? (7) The final step will be an analysis centered on the citizens’ perception of their level of HL and self-management and if this is altered when community nurses use the intervention in their nursing care. (8) Data will be condensed and presented as key themes and findings.

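### With two districts per arm, the multilevel model tested against the normal distribution would run the primary one-sided 5% test at about 7.5% to 11%, and a valid test has about 50% power, not 80%

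*Protocol article*

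**What the plan says.** The Analyses section names one class of method for the primary outcome (change in HLS-EU-Q-16 at 6 months), for health-related quality of life and for cost-effectiveness: differences "will be calculated by applying multilevel generalized linear models", unadjusted and adjusted for baseline differences, in Stata 16. It does not state the estimator, the reference distribution or the degrees of freedom.

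The number of clusters is fixed elsewhere. Under Allocation, "The remaining 4 districts are matched 1:1 in terms of geographical area", with one rural and one urban district in each arm. Under Sample Size and Power Calculation the design is described "with 4 clusters given (2 in each alternative"). That section gives the error rates ("Requiring a power of 80% and a significance level (1-sided) of 0.05"), the effect ("based on Cohen *d*>0.8") and the clustering ("assuming a coefficient of variation in cluster size of 0.25 and intracluster correlation equal to 0.05"). It concludes that "the required sample size is 37 participants in each arm (or an average of 18.5 participants in each cluster"), and then: "With an expected loss-to-follow-up of 10%, the total required sample size is 41 in each arm".

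**The concern.** A comparison of arms made up of two districts each has 4 − 2 = 2 degrees of freedom for the between-district variance, however many people are recruited. A random-intercept model then faces two difficulties. Under ML the district variance is biased downwards and is often estimated as exactly zero, so the model treats all participants as independent. Under REML the standard error is about right on average but very unstable, and the normal distribution ignores that instability.

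What is at stake is the primary claim. Ordinary differences between districts could be read as an effect of the communication model on health literacy, in a study whose stated purpose is to inform a decision on a large-scale trial.

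**Working it through.** **1. Reproducing the planned sample size.** Inputs from Sample Size and Power Calculation: d = 0.8, one-sided alpha 0.05, power 80%, ICC 0.05, coefficient of variation (CV) of cluster size 0.25, two clusters per arm.

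- Unclustered n per arm: 2 × ((1.645 + 0.842)/0.8)² = 19.32.
- Design effect with m = n/2 per district: 1 + ((1 + 0.25²)m − 1) × 0.05.
- Solving n = 19.32 × design effect gives n = 37.7, against the stated 37.
- At n = 37, m = 18.5: design effect 1.933; SE = √(2 × 1.933/37) = 0.323 SD; power = Φ(0.8/0.323 − 1.645) = Φ(0.830) = 79.7%.

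So the plan's figure is reproduced, but with normal quantiles. A two-sided 5% level gives 67 per arm and does not match.

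**2. The same inputs with the degrees of freedom that the design has.** Noncentrality is 0.8/0.323 = 2.475.

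| Reference | One-sided 5% critical value | Power at 37 per arm |
|---|---|---|
| Normal | 1.645 | 79.7% |
| t, 2 df (unpaired) | 2.920 | 49.7% |
| t, 1 df (pairs modelled) | 6.314 | 30.2% |

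More participants do not repair this. With unlimited recruitment per district the SE falls only to √(2 × 0.05/2) = 0.224, and the 2-df power reaches 73%.

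**3. Error rate under no effect.** Simulated normal outcomes, random-intercept model, four districts of 18 or 19, one-sided nominal 5%, 60,000 trials per setting (Monte Carlo standard error about 0.1 percentage point near 5%):

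| ICC | ML, normal | REML, normal | District means, t on 2 df |
|---|---|---|---|
| 0 | 5.2% | 4.0% | about 5% |
| 0.01 | 6.5% | 5.0% | about 5% |
| 0.05 | 10.3% | 7.5% | 5.0% |
| 0.10 | 13.1% | 9.5% | about 5% |
| 0.20 | 15.9% | 10.9% | about 5% |

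With uneven districts of 14 and 23, which roughly match the planned CV, the figures at ICC 0.05 are 10.6% (ML) and 7.5% (REML). Two-sided 5% tests at ICC 0.05 run at about 14% (ML) and 9.6% (REML). Adding a pair term raises the one-sided figures to 12.6% and 8.7%.

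**4. Why the two estimators differ (ICC 0.05).** Under ML the district variance is estimated as zero in 61% to 67% of trials, and the mean model SE is 0.255 against a true 0.320, about 20% too small. Under REML the mean SE is 0.317 against 0.322, but the median is 0.267. There the main fault is the normal reference, not the average SE.

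**The case against.** The strongest reply is that the article fixes only a model class and a software package. It does not say that tests will be large-sample, does not name ML and names no Stata command. An analysis plan that is not shown may specify REML with a small-sample correction, which is itself a multilevel model and consistent with the text. This much stands: a reader might infer that the plan prescribes large-sample tests and so doubles the false-positive rate for every outcome, and the documents do not support that. Doubling needs ML, a normal reference and an ICC near 0.05 together. With REML the factor is about 1.5, and at ICC zero there is no inflation. The ICC of 0.05 is a planning assumption. For EQ-5D and costs no ICC or significance level is stated, and the cost-effectiveness result is a ratio with sensitivity analyses, which an error rate does not describe.

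What the reply does not remove is the sample size. A 2-df test with these inputs cannot give 37 per arm at 80% power, since no number of participants in four districts reaches 80%. Either the test is normal-based and its level is wrong, or it is a small-sample test and the stated power is wrong.

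**Conclusion.** The point holds for the primary outcome, in conditional form. If the multilevel model is tested against the normal distribution, as the sample size calculation implies, the one-sided error at ICC 0.05 is about 7.5% (REML) to 10% to 11% (ML) instead of 5%. If a valid 2-df test is used, the power at d = 0.8 and 37 per arm is about 50% instead of 80%, or about 30% if the matched pairs are also modelled. These figures rest on normally distributed outcomes, equal variances and the protocol's own ICC. The same mechanism applies to EQ-5D and cost differences, but its size cannot be established from the document. The issue should be settled before the analysis, because the stated level and the stated power cannot both hold.

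**What to change.** - **Primary test and interval.** Use either a comparison of district-level means with a t reference on 2 df, or a linear mixed model fitted by REML with a t reference on 2 between-district df. The first holds 5% at every ICC tried. The second is conservative: in the same simulation at ICC 0.05 its one-sided error is about 1%, with power about 43%. Name one of them as primary.
- **Adjustment.** Keep arm in the model when adjusting for baseline covariates, including baseline HLS-EU-Q-16. Regressing the outcome on covariates without arm would absorb part of the effect where districts differ at baseline. For one covariate that differs between equal arms by δ within-arm SDs, a true 0.80 shrinks to about 0.80/(1 + δ²/4): 0.75 at δ = 0.5 and 0.69 at δ = 0.8 (assumed imbalances).
- **Secondary outcomes.** Use the same 2-df reference for EQ-5D and cost differences.
- **Pairs and power.** State whether the matched pairs enter the model, and restate the power as about 50% on 2 df or about 30% on 1 df.
- **Interpretation.** Present the result as exploratory. No 2-df interval removes confounding by non-randomised district.

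The programming cost is small. The real cost is precision and candour. At the planning SE of 0.323, the half-width of a 95% interval goes from 1.96 × 0.323 = 0.63 SD to 4.303 × 0.323 = 1.39 SD, and the stated power becomes less favourable.

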## Methods

### Study Design

This trial is conducted as a clustered quasi-experimental control group study with 6-month follow-up. The trial runs from November 2021 to May 2022. This study was originally designed as a 2-armed cluster-randomized controlled trial. However, the randomization protocol was abandoned after several months of unsuccessful recruitment efforts, and the study was redesigned as a quasi-experimental control group study. The primary reason for abandoning the randomized controlled trial design was challenges related to recruiting all districts making it difficult to conduct a meaningful randomization. The trial is registered at ClinicalTrials.gov (NCT04929314).

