### Outcome Measurements

#### Primary and Secondary Outcomes

The primary outcome of this study is the change in the level of HL assessed by the HLS-EU-Q-16 questionnaire [16] from baseline to follow-up at 6 months. The HLS-EU-Q-16 measures self-perceived HL and reflects the conformity between individual competencies needed to navigate the health care system and situational complexities. Hence, the HLS-EU-Q-16 reflects the self-perceived level of HL, and this should be taken into consideration when interpreting the survey results. This study hypothesizes that adding the ICM and continuity in documentation to usual community care will lead to a significantly higher level of self-perceived HL for the included participants.

Two secondary outcomes will be reported: first, the between-group difference in health-related quality of life measured by the EQ-5D-3L questionnaire [21] at follow-up after 6 months, and second, the incremental cost-effectiveness ratio representing the total cost per additional HLS-EU-Q-16 point accrued from baseline to follow-up at 6 months. This trial adopts a health- and social sector perspective with the following cost categories: intervention costs, costs associated with all hospital contacts, primary sector costs (ie, general practitioners and other primary care visits), costs associated with home nurse visits, and home care costs due to individual care and practical help as well as individual or group rehabilitation costs. Service cost components will be based on register data, that is, from the Danish National Patient Register (all hospital contacts) [22], the National Health Insurance Service Register (all primary care contacts) [23], and the electronic care register in Aalborg Municipality. All data can be unambiguously linked with the help of a 10-digit social security number that all Danish citizens have.

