A limitation of this study is the design as a quasi-experimental and abandoning the original randomization protocol. This means that this study may be subjected to selection bias, as between-group baseline characteristics may differentiate. Another limitation is the relatively short follow-up time, as between-group comparisons can only be made at the 6-month follow-up. This might be problematic since changes in particularly costs and health-related quality of life require behavior change that might take time to occur. However, recent guidance for developing and evaluating complex interventions recommends that broad-ranging evaluations are conducted in the early phases and that they also include economic evaluation. The aim is to identify the scope of cost and different effects that can help decision makers understand the potential of the intervention and decide whether proceeding to a large-scale evaluation is worthwhile [37]. In making this judgment, it is a standard health economic practice also to model the joint decision uncertainty surrounding particularly health-related quality of life outcomes and costs [38,39]. Reporting cost-effectiveness (including health-related quality of life, costs, or quality-adjusted life years) with 6-month follow-up specific to the domain of HL has also previously been reported [40,41] and to other interventions aimed at changing behavior [42,43]. The expectation is that the results of the trial therefore can create the base for deciding to conduct a large-scale study and inspire the conduction of more studies that seeks to create and evaluate interventions aimed at enhancing the level of HL and reducing the usage of health resources.

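### Covariates are chosen by observed baseline imbalance and EQ-5D-3L is defined at 6 months only; the baseline EQ-5D-3L score should always be in the model

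*Protocol article*

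**What the plan says.** The Analyses section of the protocol article states that between-group differences in health literacy, quality of life and cost-effectiveness "will be calculated by applying multilevel generalized linear models", and that "both an unadjusted and adjusted estimate controlling for meaningful baseline differences will be reported". It does not rank the two estimates.

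The section Primary and Secondary Outcomes treats the two questionnaires differently. For health literacy, "The primary outcome of this study is the change in the level of HL assessed by the HLS-EU-Q-16 questionnaire", measured over 6 months. For quality of life, the outcome is "the between-group difference in health-related quality of life measured by the EQ-5D-3L questionnaire [21] at follow-up after 6 months".

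On the design, Study Design reports that "the randomization protocol was abandoned after several months of unsuccessful recruitment efforts". Allocation adds that "The remaining 4 districts are matched 1:1 in terms of geographical area", with one district of each pair in each arm and baseline measurements completed before allocation. The Discussion concedes that "this study may be subjected to selection bias, as between-group baseline characteristics may differentiate".

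**The concern.** In a non-randomised comparison, the baseline value of an outcome is usually the first thing to adjust for. The stated rule does not secure this for EQ-5D-3L, for two reasons.

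- The outcome definition contains no baseline value, so the unadjusted estimate is a plain 6-month difference and includes whatever gap existed at the start.
- Covariates enter the adjusted model only if their baseline difference is judged meaningful. Confounding depends on imbalance and prognostic strength together. A strong predictor with a moderate gap, such as the baseline score itself, can therefore be left out.

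The covariate set also depends on the data. If the two estimates disagree, the article does not say which one carries the conclusion. At stake is the interpretation of the quality-of-life result, in a study whose authors name selection bias as a limitation.

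**Working it through.** **Inputs from the article (Sample Size and Power Calculation; Allocation).** d = 0.8, one-sided alpha 0.05, power 80%, 2 districts per arm, ICC 0.05, coefficient of variation of cluster size 0.25, 37 per arm before loss and 41 after.

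**Inputs assumed, because the article does not give them.** Baseline/follow-up correlation r = 0.3 to 0.7; baseline gap g = 0.2 to 0.5 SD; equal SDs at the two times.

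**Step 1: reproduce the plan's figure.** Without clustering, n = 2 × ((1.645 + 0.842)/0.8)² = 19.3 per arm. At 18.5 per district the equal-cluster design effect is 1 + 17.5 × 0.05 = 1.875. The correction for unequal clusters uses λ = 0.925/(0.925 + 0.95) = 0.493 and gives 1.875/(1 − 0.0625 × 0.493 × 0.507) = 1.905. Then 19.3 × 1.905 = 36.8, which rounds up to the stated 37. The figure is not in dispute; this confirms how the ICC and cluster variation enter.

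**Step 2: is a 0.3 SD gap plausible?** At baseline, with 41 per arm (20.5 per district), the design effect is 1 + (1.0625 × 20.5 − 1) × 0.05 = 2.039. The SD of the difference between arms is √(2 × 2.039/41) = 0.315 SD. Chance alone then gives a gap above 0.3 SD with probability 2 × (1 − Φ(0.3/0.315)) = 0.34, and above 0.5 SD with probability 0.11. The ICC was set for HLS-EU-Q-16 and is borrowed here for EQ-5D-3L; pair matching may make the gap smaller. This step shows only that the assumed size is ordinary. It does not measure selection bias.

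**Step 3: what each analysis does with a gap g when there is no treatment effect.** If the gap fades as individual scores do, the follow-up difference is r × g. If it is a persistent district difference, the follow-up difference is g. For g = 0.3 SD:

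| r | 6-month difference, no baseline: fading / persistent | Change score: fading / persistent | Baseline-adjusted: fading / persistent |
|---|---|---|---|
| 0.3 | 0.09 / 0.30 | −0.21 / 0 | 0 / 0.21 |
| 0.5 | 0.15 / 0.30 | −0.15 / 0 | 0 / 0.15 |
| 0.7 | 0.21 / 0.30 | −0.09 / 0 | 0 / 0.09 |

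The formulas are r × g or g; (r − 1) × g or 0; and 0 or (1 − r) × g. For g = 0.2 SD the first column runs from 0.06 to 0.14, or 0.20 if persistent. For g = 0.5 SD it runs from 0.15 to 0.35, or 0.50 if persistent.

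**Step 4: would the rule catch the gap?** The article does not define what counts as meaningful. As an illustration only, suppose it meant a two-sided 5% test ignoring clustering. With 41 per arm, a 0.3 SD gap would be flagged with probability Φ(0.3 × √(41/2) − 1.96) = Φ(−0.60) = 0.27, and a 0.5 SD gap with probability 0.62.

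**The case against.** The strongest reply is that an adjusted estimate is already promised for every outcome, never the unadjusted one alone. Naming 6 months fixes when EQ-5D-3L is compared and does not bar its baseline value from the model. A large enough baseline gap is what the rule would pick up. All of this stands. A reader might infer that the EQ-5D-3L comparison is confounded by design; the article does not support that. Carry-over is certain only for the unadjusted estimate, and possible for the adjusted one.

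A reader might also extend the point to every effect estimate. The primary outcome is a change score and already subtracts its baseline. What remains there is possible regression to the mean, in the opposite direction.

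Nor should the 0.32 SD chance gap be read as a bias. It is sampling variation, which a cluster-aware standard error already reflects. Setting it against the 0.8 SD target would be wrong as well, because that target belongs to HLS-EU-Q-16.

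It is tempting to make baseline-adjusted follow-up the sole primary analysis for HLS-EU-Q-16. Without randomisation this is a trade-off. For a persistent district gap the change score is unbiased, while adjustment leaves (1 − r) × g.

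Finally, covariate names and a threshold may well be in an analysis plan that is not shown, and their absence is not the point. The point is the selection principle that the article does state. A plan that follows it can still omit the baseline EQ-5D-3L score.

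**Conclusion.** The point holds in a limited form. Choosing covariates by observed imbalance, with the two estimates unranked and no baseline value in the EQ-5D-3L definition, leaves the quality-of-life comparison open to a starting gap that the authors themselves anticipate. For an assumed 0.3 SD gap, the carry-over is about 0.09 to 0.21 SD for r between 0.3 and 0.7, and up to 0.30 SD if the gap is a persistent district difference. It applies to the unadjusted estimate, and to the adjusted one if the baseline score is left out and no other covariate stands in for it. Both the gap and r are assumptions, and the article gives no EQ-5D-3L target against which to judge the result. It does not show that the primary result is biased. The flaw is worth correcting because the correction is nearly free; it is not fatal to the study.

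**What to change.** Amend the Analyses text on three points.

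- **EQ-5D-3L.** Always include the participant's baseline EQ-5D-3L score. The article implies that it exists, since questionnaires are returned with the consent form and baseline measurement precedes allocation, but does not name it; this needs confirming.
- **Covariates and lead estimate.** Fix a short list before the data are examined, from data already collected, and apply it whatever imbalance appears. Age, sex and the matched district pair are examples; I assume that age and sex are recorded at enrolment. Name the adjusted estimate as the lead and the unadjusted one as supportive.
- **HLS-EU-Q-16.** Keep change from baseline as the primary outcome and report the baseline-adjusted model beside it, stating that the two rest on different assumptions. Agreement strengthens the conclusion; disagreement should be reported as such.

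I do not propose adjusting for prior-period costs or number of chronic diseases, because the article does not show that either will be collected.

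The cost is wording and a few degrees of freedom among 82 participants, with no extra recruitment. The pair term deserves thought: if inference is made at district level, 4 districts less 2 arm means leaves 2 degrees of freedom, and the pair takes 1 of them. Adjustment will not remove district-level confounding with two districts per arm. A persistent 0.3 SD gap would still leave 0.09 to 0.21 SD over the same range of r, and the report should say so.
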